**Figure 3 F3:**
[figure not shown]
TDAs used according to entry sites and populations (PHC or DH). TB Speed SAM TDA will be used in children <5 years hospitalised with SAM. PAANTHER will be used in CLHIV<15 years. WHO TDA A or WHO TDA B will be used in children <15 years or children <10 years depending on the country adaptation. CLHIV, children living with HIV; CXR, chest X-ray; DH, district hospital; hosp, hospitalised; PHC, primary health clinic; SAM, severe acute malnutrition; TB, tuberculosis; TDA, treatment decision algorithm.

### SOC per country

In Mozambique, the SOC approach for child TB diagnosis relies on NTP algorithms which include: TB symptoms screening, HIV testing, Ultra testing on sputum or stool and testing with the tuberculin skin test. Urine LAM testing is indicated for CLHIV. No CXR is performed. In Zambia, the SOC follows the union’s desk guide algorithm, which involves symptom screening, HIV testing and Ultra on respiratory and stool samples. Urine LAM is more broadly used (eg, children with SAM or sepsis). CXR is performed dependent on availability. In both countries, TB diagnosis is based on symptoms, suggestive CXR or TB exposure, and TB diagnosis is confirmed if there is a positive microscopy, Ultra or LAM test result.

### Implementation strategies

Implementation strategies supporting intervention deployment will be aligned with the routine NTP implementation plans of both countries. District-level training for HCWs on TDA use, digital tool use and interpretation of imaging results will include initial face-to-face training, cascade training to other facility staff members and continuous training supported by digitalised training and support material. Monthly (first 3 months), then quarterly support supervision visits and clinical mentoring visits will be organised both on-site and online; these visits will address implementation bottlenecks and reinforce clinical skills. NTPs will lead the procurement of equipment and supplies to ensure clinicians have access to adequate sampling and testing materials and supplies for the optimal use of TDAs in the field. Continuous coordination meetings will be organised. Community mobilisation activities within facility catchment areas and districts overall will include community meetings and radio shows.

National data collection systems for childhood TB/integrated management of childhood illness will be strengthened for routine programme monitoring and for trial data collection, through the use of the DHIS2 platform on tablets. At the facility level, the EMR will be completed on tablets to report individual data for each child with presumptive TB: demographic, clinical and other data needed to calculate TDA scores and to assess disease severity. The CDSS, interconnected with the EMR module, will extract the children’s characteristics and facility profile data to orient on the choice of the TDA data and to calculate the TDA scores.

### Randomisation

In each country, health districts will be units of intervention and all will start the trial in the SOC arm. Randomisation will be done at the district level, separately for each country. For each district, the sequence will include SOC (3–12 months), intervention (3–12 months) with a lead-in/transition phase of 1 month for the stepped wedge part of the trial and then continued intervention in routine conditions with supervision (9 months) (figure 1). The randomisation list stratified by country will be generated by the trial statistician and will define the order in which each district will switch from control to intervention (every 3 months). The study coordinators will be blinded to the randomisation list and informed of the next district to switch 8 weeks prior to crossover.

### Sample size

For the effectiveness component, the statistical power to detect an increase in TB detection among children attending care (primary effectiveness endpoint) was estimated to be 0.922 for country and 0.981 for joint-analyses, using the Shiny CRT Calculator^37^ and using the following assumptions: (1) an estimated attendance of 10 500 children per quarter and per district (3000 at DH and 7500 at PHC levels); (2) a hypothesised 0.1% TB case detection rate among sick children attending care at SOC phase and 0.3% at intervention phase; (3) a discrete time decay correlation structure with a cluster auto-correlation of 0.95; (4) an intra-class correlation of 0.03 adjusted to the low prevalence of a rare binary outcome^38 39^; (4) a significance level of 5%; (5) a T-distribution applied as small sample correction for CI estimation.

Sample sizes for the acceptability, feasibility/implementation, health economics and health policy evaluations were determined as follows: (1) for HCWs (per district)—an exhaustive recruitment estimated at ~200 HCWs for the child TB and TB diagnosis questionnaires (table 1); 15 HCWs per district using digital tools for the usability questionnaire; a purposive selection of ~eight HCWs for individual interviews and of 12 HCWs per district for the time and motion study; (2) for parents/caregivers (per district): a purposive selection of 8–12 parents/caregivers for group interviews during the formative survey; of ~eight dyads (parent/caregivers-child) for individual qualitative interviews during the trial; of 240 parents/caregivers per country for patient cost surveys; (3) for key informants: a purposive selection of 5–10 stakeholders at district level and of 2–5 at provincial, national and international levels, respectively, per country.

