#### Effectiveness endpoints

For the effectiveness endpoints, data will be analysed both at trial (joint analysis) and country levels (country analysis). The primary effectiveness analysis will focus on the stepped-wedge period (five quarters) and compare all endpoints using aggregated or individual register-based data between SOC and intervention. Generalised estimating equations^40^ with fixed effects for steps and intervention will be used. Data from the transition period will be removed. We will conclude that the intervention is more effective than the control if the observed difference in outcome is statistically significant (p<0.05). Model goodness-of-fit will be assessed, and alternative solutions will be discussed and considered, if relevant. Sensitivity analysis will use the same approach but will consider data from the transition period as intervention data. Secondary analysis will be planned and performed on all districts to (1) assess TDA-based approach effectiveness on diagnostic accuracy and implementation and (2) account for secular trend and potential bias of the study effect. Subgroup analyses will be performed considering the type of vulnerability (including age group), sex, facility-level and country. Analyses will be carried out with R V.4.4 or higher.

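### The stated power (0.922 per country, 0.981 joint) does not follow from the printed ICC of 0.03; the printed inputs give at most about 0.27 and 0.48

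*Protocol article*

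**What the plan says.** The Sample size section of the protocol article says that power for the primary effectiveness endpoint "was estimated to be 0.922 for country and 0.981 for joint-analyses", and ties both figures to one list of inputs:

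- "an estimated attendance of 10 500 children per quarter and per district";
- "a hypothesised 0.1% TB case detection rate among sick children attending care at SOC phase and 0.3% at intervention phase";
- "a discrete time decay correlation structure with a cluster auto-correlation of 0.95";
- "an intra-class correlation of 0.03 adjusted to the low prevalence of a rare binary outcome";
- a 5% significance level, with sidedness not stated;
- "a T-distribution applied as small sample correction for CI estimation", with degrees of freedom not stated.

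The rest of the design is fixed elsewhere in the article. Study settings gives four districts per country. Randomisation makes the district the randomised unit, stratifies by country, and has one district switch every 3 months after a one-month transition. Effectiveness endpoints (under Data analysis) gives five quarters and a model with fixed effects for steps and intervention. It adds: "Data from the transition period will be removed". The same section plans both joint and country analyses and takes p<0.05 as the criterion for effectiveness.

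**The concern.** The article prints a result and all the main inputs to it, so a reader should be able to recover the result. An ICC of 0.03 is very large for a proportion of 0.1% to 0.3%. On the proportion scale it implies a between-district coefficient of variation of √(0.03·p(1−p))/p, which is 5.5 at p = 0.001 and 3.2 at p = 0.003. With four districts per country, that much between-district variance should leave little power.

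This is the only power statement for the primary endpoint. Country analyses are planned alongside the joint one, and Study design says the two countries are autonomous in start date and analysis. Whether a single country's result could be expected to reach p<0.05 therefore matters to how that result is read.

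**Working it through.** **Inputs.** From the article: 4 sequences × 5 quarters; 1 district per sequence (country) or 2 (joint); m = 10 500 per district-quarter; difference 0.003 − 0.001 = 0.002; autocorrelation 0.95; ICC 0.03. Assumed: a two-sided 5% test; total variance s² equal to the mean of p(1−p) over the two arms, (0.000999 + 0.002991)/2 = 0.001995; and a range of degrees of freedom (df), because none is given.

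**Model.** Generalised least squares on district-quarter means with fixed quarter effects and an intervention effect. The covariance between quarters t and t′ within a district is s²·[ICC·0.95^|t−t′| + (1−ICC)/m if t = t′]. The SE of the intervention effect comes from the inverse information matrix, and z = 0.002/SE.

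- Normal test: power = Φ(z − 1.96).
- T correction, central shift: power = P(T_df ≤ z − t_{0.975,df}).
- T correction, non-central: power = P(T_df(z) > t_{0.975,df}).

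Where two T values are shown below, they are central shift, then non-central.

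**Attempt to reproduce 0.922 and 0.981 at ICC 0.03.**

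| | SE | z | Normal | T |
|---|---|---|---|---|
| Country | 0.00148 | 1.350 | 0.271 | 0.05 / 0.13 (2 df); 0.08 / 0.16 (3 df) |
| Joint | 0.00105 | 1.909 | 0.480 | 0.31 / 0.36 (6 df); 0.35 / 0.39 (8 df) |

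Neither figure is recovered.

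**Variants at ICC 0.03 and autocorrelation 0.95** (country / joint, normal):

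- one-sided test: 0.384 / 0.604;
- block-exchangeable correlation: 0.281 / 0.496;
- variance from the control rate only: 0.479 / 0.770;
- transition month removed: 0.267 / 0.474;
- facilities as clusters (28 per country, 1500 each; not the randomised unit): 0.857 / 0.990.

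None gives 0.922 / 0.981.

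**Which ICC would give the printed pair?** More than one setting does.

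1. *ICC 0.003.* Country SE 0.000592, z = 3.378, normal power 0.922. Joint z = 4.777, power 0.981 with t on 8 df (central shift) and 0.998 with the normal.
2. *A common t on 2 df.* Country power 0.922 needs z = 4.303 + 2.225 = 6.528. Doubling the districts multiplies z by √2, to 9.232, and P(T₂ ≤ 9.232 − 4.303) = 0.981. In this model that z needs an ICC of about 0.000016 to 0.000017.
3. *0.03 read as a latent (logit-scale) value.* The between-district variance on the logit scale is (0.03/0.97)·π²/3 = 0.102. Multiplying by p(1−p) gives a proportion-scale ICC of about 0.0001 at p = 0.001 and 0.0003 at p = 0.003. Normal power then exceeds 0.999 in both analyses. With t (central shift), country power is 0.77 to 0.85 (2 df) or 0.93 to 0.96 (3 df); joint power is about 0.999 on 6 df, or 0.95 to 0.97 on 2 df. The printed pair does not appear.

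**If the ICC was 0.003.** Country power with a T correction is 0.23 / 0.46 (2 df), 0.57 / 0.62 (3 df) and 0.71 / 0.72 (4 df). Joint power is 0.971 / 0.976 (6 df), 0.977 / 0.982 (7 df) and 0.981 / 0.986 (8 df).

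**Transition month.** Suppose the month falls inside each switching quarter, so that 7000 of 10 500 children remain there. At ICC 0.003 with a normal test, country power then goes from 0.922 to 0.900.

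**The case against.** The strongest defence is that the article describes its ICC as adjusted for a rare outcome. The value 0.03 might then be a figure on another scale, or one from before adjustment, with something much smaller entered in the calculator. That is possible, and on a latent-scale reading country power can be high even with a T correction (0.93 to 0.96 on 3 df). But the sentence presents 0.03 as the value used, and the latent-scale reading does not return both printed powers either. The defence therefore explains why the printed number may not be the operative one; it does not make the paragraph correct.

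Three stronger conclusions are tempting, and the document supports none of them.

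- *That the ICC was certainly 0.003 and 0.03 is a tenfold slip.* The match is close, but it needs a normal test for one figure and t on 8 df for the other, and the 2-df setting fits the pair about as well.
- *That the two powers must rest on different distributions, since 0.922 would imply 0.998 jointly.* This holds only under a normal test. Under a common t on 2 df, 0.922 implies 0.981. Using 2 df for eight districts would be unusual, but the article does not exclude it.
- *That each country is underpowered on any T-based reading.* This depends on the ICC. It is so at 0.003 with few df, and not so at 0.0002 with 3 df.

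Nor does the article say that each country analysis is adequately powered or confirmatory, so there is no such sentence to withdraw. The transition month is a minor matter: the Randomisation section does not say where it falls relative to the quarters, and its effect is small.

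**Conclusion.** The point holds as an inconsistency between the printed inputs and the printed result. With a two-sided 5% test, districts as clusters and an arm-averaged variance, the inputs give at most about 0.27 (country) and 0.48 (joint), against 0.922 and 0.981. Any T correction lowers both. The more favourable variants tried with districts as clusters (one-sided test, control-rate variance) still fall well short.

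The operative ICC cannot be identified. The two settings that fit the printed pair have ICCs roughly 180-fold apart (0.003/0.0000165 ≈ 180), and neither is 0.03. The ICC is the natural suspect because its scale is ambiguous, but power is also sensitive to the autocorrelation: at ICC 0.03, a value of 0.995 instead of 0.95 would give 0.927 / 0.998 (normal). The true power may be higher or lower than printed. What is established is that a reader cannot tell, from this paragraph, how well powered the country analyses are.

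**What to change.** In the Sample size section:

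1. Replace the printed ICC with the value entered in the calculator, and say whether it is on the proportion or the latent scale. Confirm the autocorrelation at the same time.
2. Give the degrees of freedom used for the country and the joint analysis, and state whether the test is two-sided.
3. Recompute both powers with the same stated T-distribution and with transition-month data removed, as the analysis section specifies, and restate both figures.

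No replacement figure should be written in until the ICC is known. For orientation only, before removing the transition month: if it was 0.003, country power would be about 0.23 to 0.72 on 2 to 4 df, and joint power about 0.97 to 0.99 on 6 to 8 df.

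The cost is one rerun of the calculator and one corrected paragraph. Design and enrolment are unchanged. The stated power, especially for a single country, may become less favourable.

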Semistructured facility observations	X		X	X		X	Six-monthly	Different aspects of TB activities will be observed: service offer, HR, patient flow, management, infrastructure, equipment and stock of supplies *Tablet-based observation checklist and notes write-up on a digital recorder*
Semistructured community observations	X		X	X			Six-monthly	Observation of access and use of healthcare services (including living conditions, road conditions, transportation), identification of key stakeholders and influential leaders *Tablet-based observation checklist and notes write-up on a digital recorder*
Usability questionnaire				X			Intervention phase Six-monthly *HCW using EMR*	HCWs’ overall satisfaction, the ease of use of tools and the learning process. If possible, this will include a qualitative ‘think aloud method’ where the participants will be asked to interact with the tool while continuously verbalising their thoughts. *Self-administered REDCap questionnaire on tablet*
Group interviews	X		X	X		X	Formative phase *Facility-in-charges/site managers, parents/caregivers*	Interview guides exploring norms and attitudes towards childhood TB diagnosis, perceptions, preferences and views towards algorithms and digital health. *Group interviews conducted face-to-face*
Individual interviews	X		X	X	X	X	Quarterly (implementation and intervention) 6 monthly (acceptability) *HCWs, district focal points, parents/caregivers, community members, civil society representatives*	Interview guides exploring attitudes towards childhood TB diagnosis, perceptions, preferences and views towards algorithms and digital health *Interviews conducted face-to-face or on the phone / via video call interviews*.
Time and motion interviews					X		SOC and intervention *HCW*	Recording of all activities related to TB patients and the length of time specific staff (nurses, doctors, radiographer/radiologist/imaging specialist and laboratory technicians) spend on each activity. *Elicited and recorded by research assistants*.
Patient cost survey					X		SOC and intervention *Parents/caregivers of children receiving treatment for tuberculosis*	Recording of costs for patient families in each country. Costs are categorised into direct medical costs, direct non-medical costs and indirect costs and are collected before and during the Decide-TB intervention. *Elicited and recorded by research assistants*.

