### Endpoints

The endpoints of the different research components will be quantitative (box 1), qualitative or mixed.

Box 1Trial interdisciplinary quantitative endpoints.Effectiveness endpointsPrimary endpoint: proportion of children started on treatment for tuberculosis (TB) among sick children attending care at participant health facilities for any health complaints.Proportion of children treated for TB among those with presumptive TB, including children with microbiologically confirmed TB.Proportion of children from high-risk groups treated for TB (age <2 years, children living with HIV, children with severe acute malnutrition) among all children from high-risk group attending care and among children from high-risk groups with presumptive TB.Proportion of children with TB who are microbiologically confirmed (ie, smear or Xpert or lipoarabinomannan positive), ratio of <5 years to 5–14 years among children with TB and ratio of pulmonary TB to extrapulmonary TB.Time from presumptive TB identification to final TB treatment decision and access to TB diagnostic assessment defined as the proportion of children with presumptive TB having completed assessment with the treatment decision algorithms (TDAs) and clinical decision support systemClinical Decision Support Systems, including in high-risk groups.Concordance of the TDA result and the final TB treatment decision using the proportion of children wrongly initiated or not initiated on TB treatment defined as: (1) children not started on TB treatment despite positive score; (2) children initiated on TB treatment despite negative score.Proportion of missed TB cases and over-diagnosed TB cases (unlikely TB with a positive score) compared to a reference standard diagnosis. This will be assessed in a subset of children with full diagnostic assessment (≥1 respiratory or stool sample tested with Xpert MTB/RIF Ultra, chest X-ray (CXR) availability, clinical evaluation and follow up) at district hospital or with access to CXR.Concordance of the severity evaluation and decision for short TB treatment regimen using the proportion of (1) children with 4-month TB treatment regimen used despite severe disease as assessed by the clinical/CXR evaluation; (2) children with 6-month TB treatment regimen despite non-severe disease as assessed by the clinical/CXR evaluation.Proportion of missed severe TB cases and cases over-diagnosed as severe, compared to reference standard severity assessment by expert at low level of health care: (1) children with non-severe disease according to clinical criteria despite severe disease as evaluated by expert CXR read; (2) children with clinically assessed severe disease despite non-severe disease as evaluated by expert CXR read.Proportion of children with presumptive TB and with non-severe TB disease initiated on shorter TB treatment.TB treatment outcomes as defined per WHO (treatment success, cured, treatment completion, loss to follow-up, death, treatment failure) overall and stratified by severity and regimen duration.Deaths averted assessed through modelling.Number of adults with TB, including microbiologically confirmed TB, and proportion of all TB diagnosed that is child TB.Acceptability endpointsCo-primary endpoints: clinicians stating that in their facility they are confident in their ability to decide to initiate TB treatment in a child <5 years/in a child 5–14 years.Secondary endpoint: clinicians stating that in their facility they are confident in their ability to decide to initiate TB treatment in a child.Secondary endpoints: clinicians stating that in their facility they are not over-diagnosing children <5 years/5–14 years/all children, that is, initiating children on TB treatment when they actually do not have TB.Secondary endpoints: clinicians stating that in their facility they are supporting children <5 years/5–14 years/all children with TB to access care/medication as swiftly as they should.Feasibility and implementation endpointsCo-primary endpoint: healthcare workers (HCWs) stating that in their facility they have the adequate tools to diagnose children <5 years for TB/5–14 years for TB*.Secondary endpoint: HCWs stating that in their facility they have the adequate tools to diagnose any children (<15 years) for TB*.Secondary endpoint: clinicians stating that in the last 3 months they started a child on TB treatment.Health economics endpointsa. Cost analyses of the standard of care (SOC) and of the comprehensive TDA-based approachTotal TB care costs from the health system perspective.Unit cost per TB care activity (eg, clinical assessment, CXR).Total TB care costs of overdiagnosis (false positive)—intervention only.Total costs incurred by parents/caregivers for receiving child TB care.b. Cost-effectiveness of the comprehensive TDA-based approach compared to the SOC:Modelled health impact measure:Number of children treated for TB.Number of adults treated for TB.Number of deaths.Disability-adjusted life years (DALYs): measure of healthy life lost, either through premature death or living with disability due to illness.Cost-effectiveness measure, that is, incremental cost per:Incremental number of children treated for TB.Death averted.DALY averted.c. Budget impact of the comprehensive TDA-based approach scale-up compared to the SOC over 5 years:Cost of scaling up the comprehensive TDA-based approach nationally.Cumulative number of children and adults treated for TB, lives saved and DALYs averted during a 5-year scale-up.

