#### Health economics endpoints

Mean costs between arms will be calculated and reported descriptively alongside their 95% uncertainty intervals but will not be compared statistically. Cost analyses will be conducted following WHO guidelines.^41^ Total and unit cost per child will be examined by country and by subgroups such as CLHIV and/or SAM, type of cost inputs, type of TB care activity and by type of health facility (DH vs PHC). Household cost analysis will be conducted following WHO guidelines.^42^ The within-trial cost-effectiveness analysis will use the effectiveness endpoints (proportion of children started on TB treatment among sick children attending care, including children from high-risk groups). The cost and effectiveness results from the model will then be combined to calculate incremental cost-effectiveness ratios which will be compared with the countries’ cost-effectiveness thresholds. Once diagnostic accuracy data become available, further economic modelling will generate projections for mortality and morbidity, calculated based on DALYs, which will be used to calculate the expected overall health outcomes for patients following each alternative arm. The budget impact analysis will estimate the additional costs and savings of implementing the intervention compared with current health spending for the SOC and apply these costs to the whole population. The scale-up costs will include the upfront cost of new equipment and training as well as the running costs of TB diagnosis and treatment services.

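### The 240 caregivers per country in the patient cost survey are selected purposively, yet the survey is used for mean household costs by phase with 95% uncertainty intervals

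*Protocol article*

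**What the plan says.** In the protocol article, the Sample size section introduces the caregiver samples with "a purposive selection of 8–12 parents/caregivers for group interviews during the formative survey". The same sentence then continues, without changing the selection method, to the parent-child pairs for qualitative interviews and to "of 240 parents/caregivers per country for patient cost surveys". Grammatically the 240 can only belong to the purposive selection. The choice of word does not look accidental, because the same section describes the HCW questionnaires as recruiting all eligible staff, about 200 per district.

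Table 1 lists the patient cost survey as a health economics tool, directed at caregivers of children on TB treatment. Its costs "are collected before and during the Decide-TB intervention", so it covers both phases. Box 1 lists among the quantitative health economics endpoints "Total costs incurred by parents/caregivers for receiving child TB care". The Health economics endpoints part of Data analysis opens with "Mean costs between arms will be calculated and reported descriptively alongside their 95% uncertainty intervals", adds that no statistical comparison will be made, and says household cost analysis will follow WHO guidelines. Nothing exempts household costs from the sentence on intervals.

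**The concern.** Purposive selection is right when the aim is range and depth of views. It fits poorly when the aim is a population mean. Without a rule that gives treated children a known chance of inclusion, the sample mean estimates the cost among the families who were chosen. An interval built from the spread of those families' costs does not reflect the error made in choosing them.

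Two consequences follow. First, the level of household cost in either phase can be off by an unknown amount. Second, if the kind of family chosen changes at crossover, the SOC-versus-intervention contrast picks up a difference that the intervention did not cause. Such a change is plausible: the Implementation strategies section plans training, mentoring, supervision and community mobilisation around the switch, all of which can alter which families come to the recruiters' attention.

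If purposive here means deliberate spread over subgroups, such as HIV status, malnutrition or facility level, an unweighted overall mean would reflect the chosen mix and not the mix of treated children. The article mentions no weighting.

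**Working it through.** **No figure to reproduce.** The article gives no standard deviation, target precision or other derivation for 240, no selection criteria and no split between phases. The two illustrations below therefore rest on stated assumptions. The supply calculation uses the plan's own rates.

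**1. How selection moves a mean (assumed figures).** Let distant families cost 2 units, near families 1 unit, and let one third of treated children come from distant families.
- True mean: 1 + 1/3 = 1.33.
- A sample in which only one sixth are distant: 1 + 1/6 = 1.17.
- Ratio: 1.17/1.33 = 0.875, which is 12.5% too low.

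If this happens in one phase only, it appears as a 12.5% difference with no real change. If it happens equally in both phases, the levels are wrong but in this simple case the contrast is not.

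**2. Coverage of a nominal 95% interval under selection bias.** Let b be the bias relative to the true mean, CV the coefficient of variation of cost, and n the number per phase. Then se = CV/√n and

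coverage = Φ(1.96 − b/se) − Φ(−1.96 − b/se).

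Example: n = 120, CV = 1 gives se = 0.0913. With b = 0.10, b/se = 1.095 and coverage is 0.805.

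| n per phase (assumed) | CV (assumed) | b = 0 | b = 10% | b = 20% |
|---|---|---|---|---|
| 120 | 0.5 | 0.950 | 0.409 | 0.008 |
| 120 | 1 | 0.950 | 0.805 | 0.409 |
| 120 | 2 | 0.950 | 0.915 | 0.805 |
| 60 | 0.5 | 0.950 | 0.659 | 0.127 |
| 60 | 1 | 0.950 | 0.879 | 0.659 |
| 60 | 2 | 0.950 | 0.933 | 0.879 |

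These values ignore clustering and the finite number of treated children. Coverage runs from nominal to almost nil, depending on a bias that the interval does not show.

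**3. Supply of eligible families.** Inputs: 10 500 children per district per quarter, and detection of 0.1% under SOC and 0.3% under intervention (Sample size); four districts per country, switching every 3 months (Study settings, Randomisation); five quarters (Data analysis).
- SOC district-quarters: 1 + 2 + 3 + 4 = 10. Intervention: 4 + 3 + 2 + 1 = 10.
- SOC starts: 10 × 10 500 × 0.001 = 105.
- Intervention starts: 10 × 10 500 × 0.003 = 315. Leaving out four 1-month transitions at 31.5/3 = 10.5 starts each: 315 − 42 = 273.
- Total, transition included: 420, so 240 is 240/420 = 57% of expected starts.
- If the 9 months of continued intervention also count: 4 districts × 3 quarters × 31.5 = 378 more, total 798, and 240 is about 30%.

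On either window the sample is a sizeable share of the families but not a census, so recruiting from a list is practicable. The list exists: Table 1 and the Data collection section state that individual TB treatment register data are collected in both phases.

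**The case against.** The strongest defence is that this is a condensed article with a separate health economics analysis plan still to be written. Purposive may stand for sensible quotas by facility level and risk group, since costs are to be reported by those subgroups. The text does not say that easy-to-reach families will be chosen. That is fair as to motive, and the later plan may well define the intervals and the phase split. It cannot supply selection probabilities once recruitment has been purposive, and the selection method is stated here.

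A reader might infer more than the documents support:
- **That the intervals are invalid outright.** They are not. If selection is unrelated to cost, coverage is nominal. The plan calls them uncertainty intervals and reports them descriptively.
- **That the incremental cost-effectiveness ratios and the budget impact are distorted.** The article does not say that household costs enter the ratios. The budget impact is framed around health spending, equipment, training and running costs of services. Provider costs have their own costing study in Table 1.
- **That the bias could never be corrected.** Register data on treated children in both phases would allow respondents to be compared with, or weighted to, recorded characteristics. Only unrecorded factors would remain.
- **That SOC cannot supply the sample.** An even split of 120 per phase would exceed 105, but no split is stated. The survey is aimed at children on treatment, not only new starts, so 105 is not a ceiling. The closer the SOC sample comes to all treated children, the smaller the bias there.
- **That the time-and-motion sample needs the same remedy.** It is also purposive ("a purposive selection of ~eight HCWs for individual interviews and of 12 HCWs per district for the time and motion study"). But Table 1 names four staff groups, and with two facility levels that makes 8 strata for 12 workers, about 1.5 each. Random draws at that size gain little, and deliberate coverage of staff groups is defensible. Nor does the article state that these data yield means with intervals.

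**Conclusion.** The point holds for the patient cost survey. A purposive sample is assigned to a quantitative estimate, so mean household costs and their SOC-versus-intervention contrast can be biased, and the 95% uncertainty intervals carry no guaranteed coverage.

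The size cannot be derived from the article. The coverage losses shown rest on an assumed number per phase, cost variation and bias. The large share of treated families sampled limits how far the mean can be off, especially under SOC. The reading also assumes that the general sentence on intervals covers household costs, which is the natural reading.

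This affects a secondary, descriptive component and leaves the primary effectiveness conclusion untouched. It is a cheap improvement to a stated method, not a threat to the trial.

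**What to change.** In the Sample size section, limit the purposive wording for caregivers to the group interviews and the qualitative parent-child interviews. For the patient cost survey, state that caregivers will be recruited consecutively, or by random draw, from the TB treatment registers by district and phase. Report refusals and families not reached, and compare respondents with the register characteristics of all treated children in the same district and phase.

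State the recruitment window and the split between phases, and check the split against expected SOC supply: about 105 starts per country in the five wedge quarters, against about 315 under intervention (273 without transition months), with more if the 9 months of continued intervention are included. These figures are a check on feasibility, not a fixed target.

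The cost is a change of wording in the protocol and the health economics plan, plus a register-based list. The number of interviews stays the same. The downside is that some selected families will be harder to reach.
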